### Endpoints/Evaluation criteria

#### Primary endpoint

The primary endpoint is:The evaluation of sarcopenia prevalence for patients 70 years and older with localized or locally advanced prostate cancer before treatment initiation.

The geriatrician will screen for suspicion of sarcopenia using the SARC-F questionnaire and muscle strength assessment as recommended by the EWGSOP2 guidelines [10]. Patient whose SARC-F score is superior or equal to four out of ten are at risk of sarcopenia and will undergo muscle strength assessment. Patient with impaired muscle strength (either handgrip strength under 27 kg for men and 16kg for women or five chair stand in more than 15 seconds) are considered with probable sarcopenia [10]. To ascertain sarcopenia diagnosis, SMI will be estimated using the Appendicular Skeletal Muscle Mass (ASMM) measured with dual-energy X-ray absorptiometry (DXA) [17], adjusted for body size (ASMM/height^2^). Chosen cut-off point for low SMI indicating sarcopenia diagnosis as per EWGSOP2 guidelines is <7.0 kg/m2 [10]. Sarcopenia severity will be evaluated using Timed up and Go test and Gait speed assessment.

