### Recruitment and follow-up

#### Screening and enrollment - T0

Eligible patients will be identified by the radiotherapist and/or the urologist and/or the geriatrician. Patient over 70 years old screened with a G8 score ≤ 14/17 will be addressed to the geriatrician and benefit from full CGA and sarcopenia assessment: sarcopenia risk will be evaluated using the SARC-F questionnaire (Strength, Assistance walking, Rise from a chair, Climb stairs, and Falls questionnaire). Muscle strength will be assessed for patient at risk of sarcopenia (impaired SARC-F). For patient with probable sarcopenia (impaired muscle strength), sarcopenia diagnosis will be confirmed by measuring the skeletal muscle index (SMI). The severity of sarcopenia will also be evaluated.

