#### Follow-up – T1

A year after standard treatment completion, patient will once again benefit from CGA and sarcopenia assessment as described for T0.

Total duration of study will be 48 months, recruitment period will be 24 months and patient follow-up period, 12 months. A year after ADT end, patient will be contacted either by the geriatrician or the study coordinator to schedule the follow-up (T1). The study procedure and data collection are detailed in Table 1.

**Table 1 Tab1:** HoSAGE Study schedule of activities and procedures

	T0	Treatment phase	T1
Oncologist consultation	X	X	
Diagnosis	X		
G8 score ≤14	X		
Geriatrician consultation	X		X
Enlighten consent	X		X
Enrollment	X		X
CGA	X		X
Demographic information	X		X
Social isolation	X		X
Cognitive status (MMSE and clock drawing test)	X		X
Mood status (GDS)	X		X
Autonomy (ADL and IADL Score)	X		X
Nutritional status (BMI, MNA score and Albumin)	X		X
Mobility (OLGT, Gait speed)	X		X
Sarcopenia screening (SARC-F, Handgrip test and chair stand test)	X		X
If Sarcopenia risk suspected (SARC-F≥4/10), and Muscle strength is impaired, SMI will be measured by (DXA)^a^	X^a^		X^a^
Radiotherapy treatment (dates, dose delivered and number of fractions)		X	
Androgen deprivation therapy (dates, dose delivered, frequency, adverse events)		X	

^a^DXA assessment performed only if SARC-F score is ≥4/10 and muscle strength is impaired (either handgrip strength under 27 kg for men and 16kg for women or five chair stand test is performed in more than 15 seconds)

*CGA: Comprehensive Geriatric Assessment; MMSE: Mini Mental State Examination; GDS: Geriatric Depression Scale; ADL: Activity of Daily Living; IADL: Instrumental Activity of Daily Living; BMI: Body Mass Index; MNA: Mini Nutritional Assessment; OLGT: One Leg Balance Test; SARC-F: Strength, Assistance walking, Rise from a chair, Climb stairs, and Falls; SMI: Skeletal Muscle Index (appendicular muscular mass/seize*^*2*^*); DXA: Dual-energy X-ray*

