### Statistical considerations

#### Sample size, power, and statistical methods

Under the assumption that the prevalence of sarcopenia in older patients with prostate cancer before initiation of treatment with ADT is between 20 to 30%, according to one of the rare studies published on the subject [21], a sample size of 200 subjects allows an estimation with a width of two-sided 95% confidence interval between 0,115 to 0.131. Previous feasibility analysis showed current collaboration between urologist, radiotherapist and geriatrician should allow enrollment of the adequate number of patients during the trial period.

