## Discussion

Sarcopenia is an independent risk factor for adverse events as falls, increased hospital length of stay or readmission and death [24]. Prevalence of sarcopenia in the community was 1-33% with higher prevalence in older or acutely ill patients treated in care facilities. European Working Group on Sarcopenia in Older People (EWGSOP), discriminates two types of sarcopenia: primary, when non other cause than old age can be identified; secondary to physical inactivity (bed rest, immobility, sedentary lifestyle), to disease (like organ deficiency, inflammatory diseases, endocrinopathies or cancer) or to nutrition disorders (low protein or energy intakes, micronutrient deficiency …) [9].

Older patients are particularly at risk of sarcopenia as muscle mass decrease with age [11] and that protein-energy malnutrition is common in this age group [25].

Likewise patients with cancer often suffer malnutrition as a result of metabolic changes, mechanical blockages or abnormalities, side effects of treatment or psychosocial issues [26]. Even though malnutrition is less present in prostate cancer [27], androgen deprivation treatment leads to hypogonadism causing undesirable changes in lipid, glucose, muscle or bone metabolism leading to accelerated bone loss, osteoporosis and increased fracture risks [7, 28]. In a preliminary study we showed that muscle disorders were present before initiation of ADT in older patients with prostate cancer and an increased risk of falls at the end of ADT [29].

The aim of the HoSAGE study protocol is to evaluate the actual prevalence of sarcopenia in intermediate to high risk prostate cancer patients over 70 years old, and the incidence on sarcopenia in this population following ADT associated to radiotherapy. Using the most recent screening tool to detect sarcopenia (SARC-F) [10], the results of this study may lead to increment ADT with sarcopenia preventions programs.

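### As written, the primary analysis estimates SARC-F-detected sarcopenia, which is at or below the prevalence named in the endpoint, and the protocol contradicts itself on who has strength tested

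*Protocol article*

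**What the plan says.** **Target.** The Primary endpoint section asks for the prevalence of sarcopenia in men of 70 and older before treatment. The Discussion states the aim as "to evaluate the actual prevalence of sarcopenia in intermediate to high risk prostate cancer patients over 70 years old".

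**Who is measured.** The Primary endpoint section says "Patient whose SARC-F score is superior or equal to four out of ten are at risk of sarcopenia and will undergo muscle strength assessment". The section Screening and enrollment - T0 agrees: "Muscle strength will be assessed for patient at risk of sarcopenia (impaired SARC-F"). For muscle mass, the Table 1 footnote says "DXA assessment performed only if SARC-F score is ≥4/10 and muscle strength is impaired", and Data analysis repeats that restriction. Data analysis also makes an SMI under 7 kg/m² the mark of a proven diagnosis.

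**Who is analysed.** Data analysis puts every enrolled subject with at least a T0 evaluation into the primary analysis, whatever his SARC-F score.

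**The conflicting text.** Table 1 has a row "Sarcopenia screening (SARC-F, Handgrip test and chair stand test") marked at T0 and T1 with no condition; only the DXA row is conditional. The Secondary endpoints section also measures the chair stand at enrolment and after ADT with no SARC-F condition.

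**Precision.** The sample-size section says "a sample size of 200 subjects allows an estimation with a width of two-sided 95% confidence interval between 0,115 to 0.131", on the assumption that "the prevalence of sarcopenia in older patients with prostate cancer before initiation of treatment with ADT is between 20 to 30"%.

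**The concern.** Sarcopenia is defined in the Abstract and Background by low strength together with low muscle mass. SARC-F is not part of that definition; it only selects who is examined. A man with low strength and low SMI who scores 3 on SARC-F meets the definition but cannot be found. If he stays in the denominator, the reported prevalence is too low, and the confidence interval does not show it because it reflects sampling error only.

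The contradiction about strength testing matters in its own right. Staff who follow the text will have no grip or chair-stand result for SARC-F-negative men. Staff who follow Table 1 will. The first route also leaves holes in a secondary endpoint that is to be compared between visits for all patients.

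The same selection applies at T1, and Data analysis takes T0 as the baseline for incidence. A man who was not measured at T0 and is SARC-F-positive at T1 can be counted as a new case although no baseline SMI exists for him.

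**Working it through.** **Inputs from the protocol.** n = 200; assumed prevalence 20 to 30%; two-sided 95% CI; stated width 0.115 to 0.131 (all from Sample size, power, and statistical methods).

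**Input not in the protocol.** Se, the share of truly sarcopenic men (low strength and low SMI) who score SARC-F ≥4. It is an assumption and is shown over a range.

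**Step 1: reproduce the plan's figure.** The exact (Clopper-Pearson) limits for x of n are the 0.025 quantile of Beta(x, n−x+1) and the 0.975 quantile of Beta(x+1, n−x).
- 20%: x = 40, limits 0.1469 and 0.2622, width 0.1153.
- 30%: x = 60, limits 0.2374 and 0.3686, width 0.1313 (from unrounded limits).

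These match 0.115 and 0.131. The Wald widths (0.1109, 0.1270) and Wilson widths (0.1104, 0.1260) do not. The stated precision is therefore correct for an exact interval. Its half-width is 0.115/2 to 0.131/2, about 5.8 to 6.6 points.

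**Step 2: follow a man with SARC-F below 4.** Under the text he has no strength test. Under the text and the Table 1 footnote alike he has no DXA. Without an SMI he cannot be a proven case. He was evaluated at T0, so he is in the denominator. A SARC-F-positive man still needs low strength and low SMI to be counted, so the questionnaire can remove true cases but cannot add false ones.

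**Step 3: expected estimate.** Expected observed prevalence = p × Se, and bias = −(1 − Se) × p. It is zero only if Se = 1. Coverage below is the probability, by exact binomial summation, that the 95% CI contains the true p.

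| True p | Se (assumed) | Expected | Exact CI at expected count | Bias (points) | Coverage |
|---|---|---|---|---|---|
| 20% | 0.9 | 18% (36/200) | 12.9 to 24.0% | −2 | 92% |
| 20% | 0.8 | 16% (32/200) | 11.2 to 21.8% | −4 | 75% |
| 20% | 0.5 | 10% (20/200) | 6.2 to 15.0% | −10 | 3% |
| 25% | 0.9 | 22.5% (45/200) | 16.9 to 28.9% | −2.5 | 90% |
| 25% | 0.8 | 20% (40/200) | 14.7 to 26.2% | −5 | 67% |
| 25% | 0.5 | 12.5% (25/200) | 8.3 to 17.9% | −12.5 | 0.6% |
| 30% | 0.9 | 27% (54/200) | 21.0 to 33.7% | −3 | 85% |
| 30% | 0.8 | 24% (48/200) | 18.3 to 30.5% | −6 | 53% |
| 30% | 0.5 | 15% (30/200) | 10.4 to 20.7% | −15 | 0.1% |

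With Se = 1 coverage is about 96%. The interval also narrows as cases are missed: its width is 0.1244 at 50/200 and 0.0964 at 25/200, so the estimate looks more precise as it moves away from the truth.

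**Step 4: what could be bounded.** Low strength is necessary for sarcopenia, so a man with normal strength is a non-case without DXA. With C confirmed cases, W low-strength men without DXA, M men with no strength result, and N in the analysis:
- lower bound = C/N;
- upper bound = (C + W + M)/N.

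M must be included. The first patient was enrolled on 11/12/2019 and recruitment was open at submission, so men enrolled under the conditional text may have no T0 strength result.

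**The case against.** The Primary endpoint section attributes the pathway to EWGSOP2 guidance, so the filter is deliberate, and the word actual comes from the Discussion. This defends an endpoint labelled as screen-detected sarcopenia. It does not defend one worded as prevalence, which is how the endpoint section itself words it.

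No sentence says how men without DXA are coded. That is true, and counting them as non-cases is an inference. It is, however, the only reading that gives a prevalence in the population the protocol names for the primary analysis.

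If Table 1 governs, universal strength testing is already planned and that part is a wording reconciliation. This stands, and it makes the fix cheap. The conflict is limited to strength testing; table and text agree on DXA.

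A reader might infer stronger conclusions that the protocol does not support:
- *That the reported CI will exclude the true prevalence.* This depends wholly on an assumed sensitivity. At 0.8 with a true 25%, the bias of 5 points is below the planned half-width of about 6, and the interval at the expected count contains 25%.
- *That a definite share of incident cases will be artefacts of detection.* Any such figure needs detection rates at both visits, which the protocol does not give. Only the mechanism can be shown.
- *That the G8 ≤14 restriction is a hidden flaw.* It is stated in the Abstract and in the Participants and Screening sections. If frailer men have more sarcopenia, it would raise prevalence relative to all men of 70 and older, so it is a separate matter of labelling.
- *That the sample-size figure is wrong.* It reproduces.

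**Conclusion.** The point holds and should be fixed, though its size is not established. As written, the primary analysis estimates the prevalence of confirmed sarcopenia detected through SARC-F. In expectation that is at or below the prevalence in the endpoint and the stated aim, with equality only if SARC-F misses no case. The direction follows from the protocol, given that men without DXA are counted as non-cases. The magnitude does not: over assumed sensitivities of 0.9 to 0.5 the bias runs from −2 to −10 points at a true 20% and from −3 to −15 points at a true 30%. The planned width of 0.115 to 0.131 covers sampling error only.

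Two parts rest on no numerical assumption. The text and Table 1 disagree on who has strength tested, and incident cases can arise without a T0 SMI. How many such cases would occur is unknown.

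**What to change.** 1. Reconcile the Screening and enrollment - T0 and Primary endpoint sections with Table 1 and the Secondary endpoints section, so that handgrip and chair stand are measured in every patient at T0 and T1 whatever the SARC-F score.
2. Label the pathway result as *SARC-F-detected confirmed sarcopenia in G8 ≤14 patients*, and state that men without DXA count as non-cases in it.
3. Report it with bounds. The lower bound is confirmed cases. The upper bound is confirmed cases, plus all low-strength men without DXA, plus any man with no strength result, including those already enrolled under the conditional text.
4. State in the sample-size section that the precision applies to the screen-detected quantity.
5. Report low strength in all patients at both visits as the measure of change that does not depend on SARC-F, and flag incident cases that have no T0 SMI.

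**Cost.** A few minutes of testing per patient, for tests already marked for everyone in Table 1. The real downside is a primary result given as a range, which may be wide if many SARC-F-negative men have low strength or if many already enrolled have no strength result. DXA in SARC-F-negative men would narrow the range; it is an optional extra and not part of this low-cost change.

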#### Secondary endpoints

The secondary endpoints are:The evaluation of sarcopenia incidence in patients 70 years and older with localized or locally advanced prostate cancer a year after the end of ADT. Sarcopenia assessment will be lead at enrollment and a year after ADT end.Evaluate the evolution of the physical performances by the measurement of mobility (Timed Up and Go test, gait speed and chair stand test) at enrollment and after ADT in patients 70 years and older with localized or locally advanced prostate.Evaluate quality of life (QoL) evolution before and after ADT for patient 70 years and older with localized or locally advanced prostate with or without sarcopenia. QoL will be evaluated using EORTC QLQ-c30 questionnaires and ELD-14 module at enrollment and a year after ADT end.Evaluate impact of socio-behavioral, anthropological and geriatric factors on sarcopenia prevalence for patients 70 years and older with localized or locally advanced prostate and on its incidence after ADT. Geriatric factors such as Autonomy (score <6 on Activity of Daily Living (ADL) Scale and score <4 on Instrumental Activity of Daily Living (IADL) scale) [18], nutrition (Weight, Body Mass index (BMI), Albumin, Mini Nutritional Assessment (MNA) )[19]., cognitive status (Mini Mental State Examination (MMSE)) [16], mood (Geriatric Depression Scale (GDS)) [20], polypharmacy, and comorbidities will be assessed by CGA. Demographic information such as age, gender, presence of a caregiver, urban or countryside way of living and physical activity (number of days when patient exercise an hour at least).Evaluate impact of ADT of patients 70 years and older with localized or locally advanced prostate on sarcopenia. Oncological data such as cancer stage and anatomy; testosterone and PSA levels at enrollment and a year after ADT end; treatment protocol for radiotherapy and ADT will also be collected.

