## Background

Prostate cancer is the most common cancer for men over 60 years old worldwide according to 2020 Globocan’s data [1, 2]. For intermediate or high risks forms of prostate cancer, radiotherapy associated to androgen deprivation therapy (ADT) for 6 to 36 months is the reference treatment [3–5]. ADT induces several side effects including, anemia, alteration of physical functions, decrease of quality of life and activity [6]; in parallel, androgen inhibitors are known to be associated with metabolic effects that could result in obesity, diabetes, cardiovascular afflictions, sarcopenia or osteoporosis [7–9].

Sarcopenia is a degenerative muscle disorder characterized by loss of muscle strength and skeletal muscle mass, with or without an increase of fat mass (sarcopenic obesity) [9]. Aging, but also poor nutrition, inactivity or cancer can contribute to sarcopenia. Moreover, sarcopenia is a risk factor of early death, falls and loss of independence or/and mobility in older populations [9].

Sarcopenia screening and diagnosis are based on a combination of measures of muscle mass and muscle strength that vary according to the international guidelines and consensus [10–12]. Measures of physical performance are used to appreciate the severity of the disease.

Sarcopenia incidence in older patients is poorly known but awareness is growing among clinicians, as the criteria to diagnose malnutrition for patients 70 years and older, edited by the French High Health Authority (HAS) [13], just recently were amended to include sarcopenia. The diagnosis is based on the new updated recommendations of the revised European guidelines (EWGSOP2) [10]. Sarcopenia screening in not yet part of the guidelines on older patients’ cancer management. In this particular context, our study aims to document (1) the prevalence of muscle disorders and sarcopenia in old patients before initiation of prostate cancer treatment with ADT and radiotherapy, and (2) the occurrence and/or aggravation of muscle disorders and sarcopenia at the end of cancer treatment.

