#### Treatment Phase

Patient will benefit from standard cancer treatment for localized and locally advanced prostate cancer, i.e.: radiotherapy associated to ADT 6 to 36 months [4, 5]. Treatment phase will be handled by urologist and radiotherapist.

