#### Data analysis

The data will be analyzed using SPSS version 17.0 software. Method and analysis will be based on the Consolidated Standards Of Reporting Trials Statement (CONSORT) (http://www.consort-statement.org/consort-statement/). The patients who would be inappropriately included despite providing consent and patients who removed their consent to participate won’t be included in the final analysis. The full population (including all subjects who will be enrolled and will be at least evaluated at T0) will be included in the analysis of primary endpoint. The normality of the parameters will be estimated using frequency histograms and the Shapiro test; the baseline parameters will be presented according to the timeline of assessments: ‘Enrollment – T0’ and ‘A year after ADT end – T1’.

The SMI under 7 kg/m^2^ at enrollment and /or a year after ADT end is considered as a proven sarcopenia diagnosis. Along with incidence of sarcopenia, we will monitor evolution of SMI and/or of physical performances (handgrip strength and/or chair stand test) for diagnosed sarcopenic patient. Only patients with probable sarcopenia (SARC-F score ≥4/10 and then muscle strength impairment), will benefit from a DXA exam [10, 22, 23]. To evaluate incidence, enrollment (T0) will be considered as baseline and compared to T1 data. Changes between initial SMI and/or handgrip strength and/or chair stand test will be compared between the two groups, and the analysis of variance for repeated measurements will be performed to compare the changes in the scores over time between the 2 groups. Multivariate analysis using linear regression models will be performed to determine the association between our analyzed variables and sarcopenia occurrence. Variables relevant to the models will be selected based on their clinical significance (two-tailed with 5% significance level). The secondary endpoints will be compared for all the patients between the 2 assessments (Chi2 test or Fisher’s exact test for categorical variables and Student’s t test for continuous variables).

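### Incidence is seen only in men who survive and attend T1, and the T0–T1 comparison is not stated to be paired; if sarcopenic men are lost more often, prevalence can appear to fall and incidence can be understated

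*Protocol article*

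**What the plan says.** The Secondary endpoints section sets two readings for incidence: "Sarcopenia assessment will be lead at enrollment and a year after ADT end". The Treatment Phase section gives standard care as "radiotherapy associated to ADT 6 to 36 months". Table 1 schedules no sarcopenia assessment between T0 and T1 and lists no item for vital status or for why a man was not assessed.

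The Data analysis section makes three relevant statements:

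- The population for the primary endpoint is everyone "including all subjects who will be enrolled and will be at least evaluated at T0". No population is named for the secondary endpoints.
- On incidence: "To evaluate incidence, enrollment (T0) will be considered as baseline and compared to T1 data".
- On the secondary endpoints generally: "The secondary endpoints will be compared for all the patients between the 2 assessments", using Chi2 or Fisher's exact test for categories and Student's t test for continuous variables. Pairing is not mentioned.

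The article also states twice that the outcome is linked to survival. The Background says that "sarcopenia is a risk factor of early death, falls and loss of independence or/and mobility in older populations". The Discussion says "Sarcopenia is an independent risk factor for adverse events as falls, increased hospital length of stay or readmission and death".

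**The concern.** The men are 70 or older with a G8 score of 14 or less, and the gap between readings is long. A man who becomes sarcopenic and then dies, or can no longer attend, is never counted as a case. If the outcome affects who is seen at T1, two different problems follow:

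- **Prevalence.** If every T0 man is compared with those who attend T1, losing men who were already sarcopenic lowers T1 prevalence although nobody has improved.
- **Incidence.** If new cases are lost more often than men who stay free of sarcopenia, the proportion seen among attenders is too low.

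The second aim, occurrence or worsening after treatment, rests on these comparisons. The Abstract even lists the relation between ADT and sarcopenia incidence as a primary objective, although the endpoint section places incidence among the secondary endpoints. The results are meant to inform a prevention plan, and a spurious absence of increase would argue against one.

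**Working it through.** **The plan's own figure.** The only precision stated is for T0 prevalence: N = 200, prevalence 20% to 30%, 95% interval width 0.115 to 0.131. Exact (Clopper-Pearson) intervals at 40/200 and 60/200 have widths 0.1153 and 0.1313, so the figure reproduces. It concerns T0 only and is not affected.

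**Timing.** From the start of ADT to T1: 6 + 12 = 18 months to 36 + 12 = 48 months.

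**Inputs.** T0 prevalence of 20% to 30% is the article's planning range. The article gives no death, dropout or attendance rates and no incidence rate. All of those below are assumptions.

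**1. Prevalence, all T0 men against T1 attenders, nobody changes.** Let p be T0 prevalence, Ls the loss among men sarcopenic at T0 and Ln the loss among the others.

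T1 prevalence = p(1 − Ls) / [p(1 − Ls) + (1 − p)(1 − Ln)]

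| Loss: sarcopenic / other | p = 20% | p = 25% | p = 30% |
|---|---|---|---|
| 5% / 10% | 20.9% | 26.0% | 31.1% |
| 10% / 10% | 20.0% | 25.0% | 30.0% |
| 20% / 10% | 18.2% | 22.9% | 27.6% |
| 30% / 10% | 16.3% | 20.6% | 25.0% |
| 50% / 10% | 12.2% | 15.6% | 19.2% |

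Example at p = 25%, 30% / 10%: 0.175 / (0.175 + 0.675) = 20.6%. At 35% / 15%: 0.1625 / (0.1625 + 0.6375) = 20.3%. In that last setting, (0.25 × 0.80 − 0.1625) / 0.6375 = 5.9% of attending men free of sarcopenia at T0 could become cases and T1 prevalence would still read only 25%.

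An unpaired chi-square test at p = 25% gives a p-value of 0.315 for 30% / 10% and 0.03 for 50% / 10%.

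**2. The same men at both visits, nobody changes.** At 30% / 10%, attenders have prevalence 20.6% at T0 and 20.6% at T1. The false fall disappears.

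**3. Incidence among men free of sarcopenia at T0.** Let i be true incidence, Lc the loss among new cases and Ln the loss among the rest.

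Observed incidence = i(1 − Lc) / [i(1 − Lc) + (1 − i)(1 − Ln)]

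With i = 15%:

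- 10% / 10%: 0.135 / (0.135 + 0.765) = 15.0%
- 30% / 10%: 0.105 / (0.105 + 0.765) = 12.1%
- 50% / 10%: 0.075 / (0.075 + 0.765) = 8.9%
- 5% / 10%: 0.1425 / (0.1425 + 0.765) = 15.7%

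With i = 20%, loss of 30% / 10% gives 16.3%, 50% / 10% gives 12.2% and 5% / 10% gives 20.9%.

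**4. Bounds for i = 15%, loss 30% / 10%.** Share of men at risk seen as cases: 0.105. Share lost: 1 − 0.870 = 0.130. Counting the lost as all non-cases gives 10.5%. Counting them as all cases gives 0.105 + 0.130 = 23.5%. The true 15% lies inside.

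**The case against.** **The unpaired reading is not established.** The Data analysis section reserves the all-T0 population for the primary endpoint, speaks of changes from baseline and names a repeated-measures analysis of variance. Student's t has a paired form, and the phrase about all patients may only mean both sarcopenia groups together. This stands in part: the text permits a paired analysis. It does not state one, though, and the named Chi2 and Fisher tests are for independent samples. The repeated-measures analysis covers scores, not sarcopenia status.

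**Rules for death and non-attendance may sit in the full protocol or SAP.** That is right, and their absence from an article is not the finding. The point rests on what the article fixes: incidence read only at T1, and a comparison worded so that two different sets of men can be compared.

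**The effect may be lost in the noise.** At 30% / 10% loss the false fall is far from significant. In the incidence example, 150 men at risk leave about 130 attenders, and 12.1% has an approximate 95% interval of 6.5% to 17.7%, which includes 15%. This is true, but the bias affects the estimate and does not shrink with a larger sample.

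**Stronger readings a reader might infer.** One is that incidence is certainly understated. The documents do not support that: they give no loss rates, equal loss gives no bias, and lower loss among cases reverses its sign. Another is that deaths among men already sarcopenic at T0 bias incidence. They do not, because those men cannot become new cases; they affect only the unpaired prevalence comparison.

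**Conclusion.** The point holds conditionally. New cases are visible only in men who survive and attend T1, and the comparison as written does not guarantee that the same men are compared. The article's own statements make higher loss among sarcopenic men plausible but do not quantify it.

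Under the assumed loss of 30% against 10%, the unpaired comparison shows prevalence falling from 25% to 20.6% with no man improved, and a true incidence of 15% reads 12.1%. Pairing removes the first error entirely. It does not remove the second, which depends on new cases being lost more often than others.

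The calendar is a further reason for missing T1 visits, separate from death: "Total duration of study will be 48 months, recruitment period will be 24 months and patient follow-up period, 12 months". A man enrolled at month 24 with 36 months of ADT would reach T1 at 24 + 36 + 12 = month 72. The calendar and the treatment durations must be reconciled.

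**What to change.** - **Data analysis section.** State that T0–T1 comparisons use men with both assessments and paired methods (for example McNemar's test for status and a paired t test for continuous measures).
- **T1 contact, already planned.** Record for every T0 patient whether he is alive without sarcopenia, alive with sarcopenia, dead, or alive but not assessed, with the reason.
- **Incidence.** Report it among assessed men who were free of sarcopenia at T0, with bounds that count the lost sarcopenia-free men as all non-cases and as all cases (10.5% to 23.5% in the example).
- **Supporting results.** Show sarcopenia or death beside the incidence, and tabulate T0 characteristics by T1 state.

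A competing-risk proportion over all men free of sarcopenia at T0 should not be presented as the corrected incidence. A man who becomes sarcopenic and dies undetected counts there only as a death. If the losses in the example are deaths, it gives 10.5%, further from the true 15% than the 12.1% in attenders.

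The cost is a little extra data entry at an existing contact and modest extra analysis. The stated uncertainty becomes wider, and the composite includes deaths unrelated to muscle, which is why it supports the incidence result and does not replace it.
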